### Data collection and management

Data will be collected by the local investigator at each site and stored anonymously in a Good Clinical Practice proof digital database (Castor EDC, Cewit B.V). Two independent monitors will perform source data verification and assess performance of study procedures at each site following a predefined schedule.

## Outcome measures and statistical analysis

### Primary outcome

The primary outcome is bacterial (re) infection within 28 days after finishing antimicrobial therapy, defined as clinical symptoms of infection and fever (>38.0°C) or hypothermia (<36.0°C) and elevated inflammatory parameters with a need for prolonged antimicrobial therapy for more than 48–72 hours. Proven or suspected viral infection, for which no antibiotics are initiated or antibiotics are stopped within 48–72 hours (after return of culture and/or viral results) are not considered as a bacterial (re) infection. A chart will aid in decision making with respect to differentiation between bacterial infection and other causes. Both per-protocol analysis and intention-to-treat analysis will be performed. A p<0.025 will be considered as significant. Regarding the primary outcome, 28-day cumulative bacterial infection rate; proportions will be defined and used to compare both treatment strategies. Subgroup analysis will be performed on late preterm neonates (gestational age 35–37 weeks). Further, mixed-effect models will be used to take into account the multiple centres.

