### Participants

Neonates are eligible for participation if they have a postmenstrual age of 35 weeks or more, are 0–28 days old, have a body weight of at least 2 kg and have a ‘probable bacterial infection’ based on clinical symptoms or maternal risk factors and elevated inflammatory parameters for which the paediatrician has decided to complete a full course of intravenous antibiotics. A C reactive protein (CRP) level of ≥10 mg/L is considered as elevated. For procalcitonin (PCT), we refer to the age-adapted ranges.^15 16^ Clinical symptoms can be found in the online supplementary material. All neonates with a proven bacterial infection, for example, positive blood or cerebrospinal fluid culture or a severe clinical sepsis requiring intensive care treatment are excluded from participation. Inclusion and exclusion criteria are described in table 1. Participants will be screened by the local paediatrician or investigator and randomised after 48 hours of intravenous treatment once informed consent has been obtained.

**Table 1 T1:** Inclusion and exclusion criteria Reduction of intravenous Antibiotics In Neonates study

Inclusion criteria	Exclusion criteria
Neonates, postmenstrual age ≥35+0 weeks, postnatal age of 0–28 days, body weight ≥2 kg. Probable bacterial infection defined as clinical symptoms and/or maternal risk factors and elevated inflammatory markers for which empiric broad-spectrum antibiotic treatment was initiated and needs to be continued for >48 hours. Clinically well. Tolerate oral feeding without overt vomiting.	Proven bloodstream infection. Absence of blood culture. Severe localised infection (meningitis, osteomyelitis, necrotising enterocolitis). Severe clinical sepsis (compromised circulation, need for mechanical ventilation). Continuous need for a central venous line. Severe hyperbilirubinaemia exceeding the exchange level. Parents’ inability to administer medication.

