### Randomisation and blinding

Participants will be randomised after 48 hours of intravenous treatment by a web-based programme according to a stratified block randomisation (stratified per site in alternated blocks of 2 and 4). Randomisation ratio will be 1:1. Randomisation can under no circumstances be influenced by the study team. If parents want their child to be in a specific group, they will be excluded from participation. Patients and healthcare professionals will not be blinded, because of the nature of treatments (intravenous vs oral therapy); the primary investigators performing the statistical analysis will be blinded for the allocated treatment.

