## Discussion/conclusion

Prolonged hospitalisation for intravenous therapy is still common practice in high-income societies when neonatal bacterial infection cannot be ruled out despite negative cultures. In-hospital treatment has a high impact on both patient and parents since prolonged hospitalisation often leads to infant–parent separation. Initiatives to prevent separation through the reduction of admission days are of increasing interest. The additional value of other biomarkers besides CRP, such as PCT, in order to rule out bacterial infection has been evaluated. A recent study showed that using PCT values as guidance for antibiotic therapy in neonates with a suspected bacterial infection leads to a reduction in days on therapy and hospitalisation. However, when the infection could not be ruled out, as is the case in infants with a probable infection, therapy was still continued intravenously for 7 days.^26^ We propose the first randomised controlled trial in a high-resource setting with a non-inferiority study design in order to demonstrate that oral antibiotic switch therapy is as effective as intravenous treatment in neonates with a probable bacterial infection. Furthermore, we will be the first to perform PK/PD analysis on oral amoxicillin/clavulanic acid on a large sample size. Once proven that serum concentrations following oral administration are adequate, and non-inferiority of oral switch has been proven, oral switch therapy could potentially be expanded to clinically well infants with a proven infection.

This study has some limitations, the most important limitation relating to the primary outcome assessment. As mentioned in the methods section, only neonates with a probable bacterial infection will be included. It is impossible to state whether or not a second infection is a reinfection or that it is caused by a different pathogen. We, therefore, developed a list of recommended diagnostics that should be determined when a participant returns with signs of a possible infection. Those results can be used for correct and uniform assessment of the event and will help differentiating between a true bacterial infection, a probable bacterial infection or a viral infection.

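### The primary outcome has no route for culture-proven infection at normal temperature, does not address early death, and uses a 48–72 hour range as its cut-off in both directions

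*Protocol article*

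**What the plan says.** The primary outcome is "bacterial (re) infection within 28 days after finishing antimicrobial therapy". The section Primary outcome of the protocol article defines an event as clinical symptoms together with "fever (>38.0°C) or hypothermia (<36.0°C) and elevated inflammatory parameters with a need for prolonged antimicrobial therapy for more than 48–72 hours". It gives no alternative route through a positive culture and does not mention death.

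The next sentence sets the non-event rule. Its scope is "Proven or suspected viral infection, for which no antibiotics are initiated or antibiotics are stopped within 48–72 hours", and it ends by saying that episodes in which "antibiotics are stopped within 48–72 hours (after return of culture and/or viral results) are not considered as a bacterial (re) infection".

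Two aids are described. In the same section, "A chart will aid in decision making with respect to differentiation between bacterial infection and other causes". The Discussion adds a list of recommended diagnostics, whose results "will help differentiating between a true bacterial infection, a probable bacterial infection or a viral infection". The content of neither is shown, and neither is said to override the definition.

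On blinding, the section Randomisation and blinding says "Patients and healthcare professionals will not be blinded, because of the nature of treatments". Only the investigators doing the statistical analysis are blinded.

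**The concern.** Two features of the definition can misclassify events.

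- **The criteria are cumulative.** A positive blood or cerebrospinal fluid culture is the clearest evidence of bacterial infection, yet it does not make an event unless the temperature is also above 38.0 °C or below 36.0 °C. An infant who dies of infection early has no stated classification.
- **The duration threshold is an interval.** It is used as a lower bound for events and as an upper bound for viral non-events. Courses that end inside the interval are those stopped or continued once culture and viral results return, and the clinicians who decide this know the arm.

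The trial expects very few events, and the same definition is used elsewhere. Primary outcomes trigger the interim analysis and feed its stopping rule. Readmission costs are counted only for a (re)infection so defined, and the cost-effectiveness ratio is expressed per (re)infection avoided. A proven infection that goes uncounted is lost from all of these.

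**Working it through.** **1. Clause by clause**

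| Case | Event rule | Viral non-event rule | Status as written |
|---|---|---|---|
| Positive blood culture, symptoms, raised markers, 37.5 °C, long course | Temperature element fails | Does not apply | Not an event |
| Death from infection before 48 h of antibiotics | Turns on how the need for longer therapy is judged | Does not apply | Not addressed |
| 60 h course, other elements met, viral infection proven or suspected | Met if the lower end (48 h) is used | Met if the upper end (72 h) is used | Meets both rules |
| 60 h course, other elements met, no viral infection suspected | Met at 48 h, not at 72 h | Does not apply | Undetermined |

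**2. The plan's own sample size** (Power calculation: 1% in both arms, margin 3%, one-sided alpha 0.025, power 90%)

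n per arm = (1.960 + 1.282)² × 2 × 0.01 × 0.99 / 0.03² = 231.16. The article states 231; strict rounding up gives 232. The figure reproduces, and this point does not change it.

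**3. Expected events**

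550 × 0.01 = 5.5 in total, or 275 × 0.01 = 2.75 per arm.

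**4. How far one infant can move the result** (275 per arm, 3 control events)

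Non-inferiority holds if the upper limit of the two-sided 95% interval for intervention minus control is below 3%. The article names no interval method, so two are shown. The Wald limit is d + 1.96 × √[(p₁(1−p₁) + p₂(1−p₂))/275].

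- 5 intervention events: 0.0073 + 1.96 × 0.01021 = 0.0273, pass.
- 6 intervention events: 0.0109 + 1.96 × 0.01081 = 0.0321, fail.

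The score limits are 2.7% with 4 intervention events (pass) and 3.2% with 5 (fail).

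The largest passing count is therefore 4 by score and 5 by Wald. At 231 per arm it is 3 and 4.

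**5. Similar under-counting in both arms (illustration)**

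The captured share s is an assumption; the documents give no figure. With true rates at the margin (1% and 4%), the observed rates are 0.01s and 0.04s, and

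P(non-inferiority declared) = Φ[(0.03 − 0.03s)/SE − 1.96].

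For s = 0.8 and 231 per arm: SE = √[(0.008 × 0.992 + 0.032 × 0.968)/231] = 0.01298, and Φ(0.006/0.01298 − 1.96) = Φ(−1.50) = 6.7%.

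| Captured share | 231 per arm | 275 per arm |
|---|---|---|
| 100% | 2.5% | 2.5% |
| 90% | 4.1% | 4.3% |
| 80% | 6.7% | 7.3% |
| 50% | 31% | 35% |

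These values use the normal approximation. Exact enumeration of the Wald rule at 231 per arm gives higher values, 4.9% at full capture and 11.7% at 80%, in the same direction.

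**The case against.** **The aids may settle these cases.** The decision chart or the diagnostics list could cover culture-positive or borderline episodes. Their content is not shown, so this limits confidence. Even so, they are described as aids, and the definition as printed would still govern.

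**Early death is not excluded.** A reader might infer that rapidly fatal infections are left out. The text does not support that: it speaks of a need for prolonged therapy, not therapy received, and an assessor could judge that need met in an infant who dies early. The gap is silence, not exclusion.

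**The contradiction is limited.** A reader might infer that every infant treated for 48–72 hours is both an event and a non-event. The non-event rule covers only proven or suspected viral infection. For other infants the status is undetermined, not contradictory.

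**Missed events do not always favour non-inferiority.** Events missed only in the control arm raise the observed difference and work against the claim. Attenuation follows when both arms lose similar shares. The documents give no evidence of differential loss.

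**A one-infant boundary exists under any definition** when events are this rare. That stands. Sparsity is not itself the fault, but it makes an unclear rule costly.

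**The entry definition has no temperature requirement.** Infants are enrolled "based on clinical symptoms or maternal risk factors and elevated inflammatory parameters", and a reader might infer that the outcome should drop temperature as well. That does not follow. Maternal risk factors do not carry over naturally to an infection weeks later, and a stricter outcome is a legitimate choice between sensitivity and specificity. Less specific events can also dilute a true difference. If the rate rose to 2% in both arms, power would be 71% with 275 per arm, and 458 per arm would be needed for 90%.

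**Conclusion.** The point holds in three parts.

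- On the natural reading, a culture-proven infection at normal temperature does not count.
- The definition does not say how death from infection before the duration threshold is classified.
- The duration cut-off is a range used in opposite directions. The two rules overlap when viral infection is proven or suspected and leave the status open otherwise, in a trial where unblinded staff set the duration.

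The number of infants affected cannot be estimated from the documents, because they do not give the share of proven infections without abnormal temperature. The false non-inferiority figures therefore show sensitivity to an assumed capture share that is equal in both arms; they do not forecast a bias. What rests on the plan's own numbers is that about 5.5 events are expected and that one reclassified infant can reverse the conclusion near the boundary, whichever interval method is used.

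**What to change.** In the outcome definition and the decision chart:

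1. Count as a primary event, regardless of temperature or antibiotic duration, (a) any positive blood, cerebrospinal fluid or other normally sterile-site culture treated as infection, and (b) any death attributed to infection.
2. Reconcile the two 48–72 hour phrases into one identical cut-off, so that the event rule and the viral non-event rule meet without overlap or gap. The choice of hours is the sponsor's.
3. Keep the temperature criterion for culture-negative episodes.
4. State that the definition governs where the chart or the diagnostics list differs from it.

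The change is to wording and needs no new data. The cost is a possible slight rise in the event count, with some loss of power against the assumed 1%. By the plan's own approximation with 275 per arm, power is 94% at 1% in both arms and 82% at 1.5%. The latter would need about 1.4 extra events per arm (275 × 0.005).

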### Follow-up

Neonates will only be discharged from the hospital if they have shown to tolerate the oral antibiotic treatment for at least two doses and are clinically well. Parents will be interviewed by telephone on the first day after discharge and on day 14 after initiation of antibiotic therapy by the local study investigator or research nurse. The local investigator will assess antibiotic intake, signs of infection, side effects and events. In addition, parents will receive a survey on day 7 and day 21 with questions regarding possible signs of infection, side effects, QOL, loss of productivity, and cost-effectiveness and demographic data (maternal, paternal age, highest level of education, socioeconomic status and siblings). All surveys are available as online supplementary material. The primary outcome of the study is assessed 28 days after treatment completion, when the patient will be seen by the local investigator or research nurse for a final visit at the outpatient department. Parents of participants in the oral treatment group will be asked to return the bottle with remaining antibiotic suspension in order to evaluate medication adherence through measurement of the remaining amount of medication present in the bottle. Follow-up of neonates in the control group will be identical.

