### Power calculation

Relapse of proven GBS infection is estimated to occur in 0%–8% of patients, but may be caused by a different strain.^17^ Two epidemiological studies estimated the recurrence rate to be 1% in proven bacterial neonatal infections.^18 19^ The current study focuses on probable infections (in which the recurrence rate is likely even lower, although evidence for this is lacking). The incidence of community-acquired late-onset sepsis in otherwise healthy neonates is low (~0.28 per 1000 live births).^20^ Therefore, we assume a 1% infection rate (including new non-related infections) in both groups. Based on a non-inferiority margin of 3% (minimum success rate 96%), 2×231 patients are needed for a power of 90% using a one-sided alpha of 0.025. Because of the first 30 patients undergoing PK measurements and uncertainty about the PK values, and potential drop-out or withdrawal (estimated approximately 5%–10%), we will include 2×275 neonates (total=550). A post hoc report on the design effect will be included.

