#### Interim analysis

A formal interim analysis will be performed after occurrence of the first four primary outcomes. The data safety monitoring board (DSMB) will assess the results and it will be determined whether the occurrence of the primary outcome was related to the index suspected bacterial infection or more likely to be an unrelated infection. The outcome of that interim analysis will determine after how many primary outcomes the next interim analysis will be performed. When more than 75% of related cases occur in the intervention arm in two consecutive interim analyses, the study will be stopped prematurely.

Secondary outcomes and their statistical analyses are described below.

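### No masked classifier is named for the primary outcome or the relatedness call in this open-label trial, and a swing of two to four called events, depending on method, can reverse the non-inferiority conclusion

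*Protocol article*

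**What the plan says.** Study design calls the trial open label. Randomisation and blinding says that patients and healthcare professionals are not blinded and names one blinded role: "the primary investigators performing the statistical analysis will be blinded for the allocated treatment".

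Follow-up says the primary outcome is assessed 28 days after treatment completion, when "the patient will be seen by the local investigator or research nurse for a final visit". Data collection and management has the local investigator collecting the data at each site.

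Primary outcome requires all of the following: clinical symptoms, fever or hypothermia, raised inflammatory parameters, and a need for antibiotics beyond 48–72 hours. Proven or suspected viral episodes do not count if antibiotics are not started or are stopped within that window. On making this distinction the section adds: "A chart will aid in decision making with respect to differentiation between bacterial infection and other causes".

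Under Interim analysis the DSMB reviews the first four primary outcomes and it is determined "whether the occurrence of the primary outcome was related to the index suspected bacterial infection or more likely to be an unrelated infection". The trial stops early if more than 75% of related cases fall in the intervention arm at two consecutive interim analyses. No masking is mentioned for this call.

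Under Power calculation, "we assume a 1% infection rate (including new non-related infections) in both groups", the margin is 3 percentage points, and "2×231 patients are needed for a power of 90% using a one-sided alpha of 0.025". Enrolment is raised to 275 per arm.

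**The concern.** Two of the four endpoint components are measured: temperature and inflammatory markers. The other two, and the exclusion of suspected viral episodes, depend on interpretation or on a treatment decision. The people the article places at that point know which arm the infant is in. Blinding the analyst protects the analysis but not a classification already in the data.

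The influence could run either way. Extra vigilance for infants treated by mouth at home would add intervention events. Reluctance to record a failure of the oral switch would remove them. In a non-inferiority trial the second is the more dangerous, because it makes a false claim of non-inferiority more likely.

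The relatedness judgement has the same exposure, and the 75% rule is applied to very few cases.

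**Working it through.** **Inputs (Power calculation; Randomisation and blinding).** Event rate 1% in both arms, margin 3 points, one-sided alpha 0.025, power 90%, allocation 1:1, 231 per arm powered, 275 per arm enrolled. The article names no test or interval method, so two are shown.

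**Step 1: the plan's own figure.** Unpooled normal approximation:

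n = (1.960 + 1.282)² × 2 × 0.01 × 0.99 / 0.03² = 231.2 per arm. The stated 231 is reproduced.

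**Step 2: expected events.** 231 × 0.01 = 2.3 per arm; 275 × 0.01 = 2.75 per arm, or 5.5 in 550. At 275 per arm, one event moves the difference by 1/275 = 0.36 points.

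**Step 3: which counts show non-inferiority.** Let x1 and x0 be the intervention and control events, and p̂1 = x1/n, p̂0 = x0/n.

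- Wald: upper limit = (p̂1 − p̂0) + 1.96 × √[p̂1(1−p̂1)/n + p̂0(1−p̂0)/n]; non-inferior if below 3%.
- Farrington–Manning: z = (p̂1 − p̂0 − 0.03)/SE, with SE from the maximum-likelihood rates constrained to differ by 0.03; non-inferior if z < −1.96.

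Examples:

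- Farrington–Manning, 4 v 2, n = 275: the constrained rates are 0.0346 and 0.0046, so SE = 0.01174 and z = (0.00727 − 0.03)/0.01174 = −1.94. This fails.
- Wald, 6 v 2, n = 275: difference 0.01455, SE 0.01019, upper limit 0.01455 + 1.96 × 0.01019 = 3.45%. This fails.

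| Intervention v control | FM z, n = 275 | Wald upper, n = 275 | FM z, n = 231 | Wald upper, n = 231 |
|---|---|---|---|---|
| 2 v 2 | −2.59 pass | 1.42% pass | −2.32 pass | 1.69% pass |
| 3 v 2 | −2.26 pass | 1.95% pass | −1.97 pass | 2.32% pass |
| 4 v 2 | −1.94 **fail** | 2.46% pass | −1.62 **fail** | 2.93% pass |
| 5 v 2 | −1.61 **fail** | 2.96% pass | −1.28 **fail** | 3.52% **fail** |
| 6 v 2 | −1.30 **fail** | 3.45% **fail** | −0.94 **fail** | 4.11% **fail** |
| 3 v 3 | −2.45 pass | 1.74% pass | −2.17 pass | 2.06% pass |
| 4 v 3 | −2.13 pass | 2.24% pass | −1.84 **fail** | 2.66% pass |
| 5 v 3 | −1.82 **fail** | 2.73% pass | −1.51 **fail** | 3.24% **fail** |
| 6 v 3 | −1.51 **fail** | 3.21% **fail** | −1.19 **fail** | 3.82% **fail** |

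At 275 per arm, starting from an equal split, Farrington–Manning needs two extra intervention events to reverse the conclusion. Wald needs four from 2 v 2 and three from 3 v 3. At 231 per arm, Wald needs three from 2 v 2 and two from 3 v 3; Farrington–Manning needs two from 2 v 2 and only one from 3 v 3.

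**Step 4: how often two calls would matter (exact binomial enumeration).**

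- True rates 1% v 1%: the probability that non-inferiority is shown but would be lost with two more intervention events is 23% (Wald) or 37% (Farrington–Manning) at 275 per arm, and 34% or 43% at 231.
- True rates 4% v 1%, the edge of the margin: leaving out two intervention events raises false non-inferiority from 4.6% to 15.7% (Wald) or from 1.9% to 8.1% (Farrington–Manning) at 275 per arm. At 231 the rise is from 4.9% to 18.0% or from 2.0% to 9.9%.

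**Step 5: the stopping rule.** Suppose three of the first four events are in the intervention arm. If all four are called related, the share is 3/4 = 75%, which is not above 75%. If the control case is called unrelated, it is 3/3 = 100%. One relatedness call decides whether the threshold is crossed at that look, although the rule needs two consecutive looks.

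**The case against.** **Nobody is named as final classifier.** The sentence about the chart is passive, and the Discussion mentions a list of recommended diagnostics for uniform assessment without saying who applies it. A reader might infer that the plan hands the final bacterial yes/no decision to unblinded local staff and excludes central review. The document does not go that far. What stands is that it does allocate roles: outcome assessment sits with local staff, blinding sits with the analysis, and no masked classifier appears. The full protocol or a DSMB charter might add one.

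**The endpoint is not purely subjective.** Fever or hypothermia and raised markers are both required, diagnostics are recommended, and independent monitors verify source data. These limit discretion but mask nobody, and they leave the symptom, duration and viral calls open.

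**The event swing depends on the method.** A reader might infer that two events always suffice. They do not. With Wald limits, which match the sample-size formula, 4 v 2 and 5 v 3 both pass at 275 per arm. Fragility at small counts also comes from the 1% rate and would exist under any blinding; masking matters because it removes one source of such swings.

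**The reinfection limitation is a different matter.** A reader might infer that the authors' own statement, that a true reinfection cannot be told from a new infection, undermines the primary outcome. It does not: the endpoint and its 1% rate include unrelated new infections. The limitation bears only on the DSMB's relatedness call. It stems from the sterile index cultures, which masking would not cure.

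**Conclusion.** The point holds as a design weakness that should be corrected. As written, the plan leaves the symptom and bacterial-versus-other calls, and the relatedness call behind the stopping rule, open to knowledge of the arm, and blinds only the step after classification. With 2 to 3 events expected per arm, a swing of two to four intervention events from an equal split is enough to reverse the conclusion at 275 per arm: two with Farrington–Manning, three or four with Wald.

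This rests on the assumed 1% rate, the 3% margin, complete follow-up of 275 per arm (231 is shown as the lower case, since 5%–10% drop-out is expected), and an analysis by one of the two methods shown. It shows how much influence a few calls could have. It does not show that bias will occur or in which direction.

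**What to change.** For each suspected episode up to 28 days after treatment, the site completes the existing chart and recommended diagnostics and sends a summary with arm, route and discharge date removed. The primary investigators who are already to be blinded classify bacterial infection yes or no against the Primary outcome definition. Anyone who receives unmasked serious adverse event reports is excluded, since Safety consideration sends these to the principal investigator. The masked classification is used for the primary analysis, and the local classification is reported as a sensitivity analysis.

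The DSMB makes its relatedness call from the same masked summary before arm-level data are shown. Its clinicians should not be the default endpoint classifiers, because they go on to see the counts by arm.

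The cost is redaction and a few hours of review for a small number of episodes; 5.5 endpoint events are expected, plus suspected episodes that turn out not to qualify. No new staff are needed. The remaining limit should be stated in the plan: a masked reader still receives antibiotic duration as decided by a treating doctor who knew the arm.
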